**Fig. 3 Fig3:**
[figure not shown]
Timeline of the quantitative evaluation of conversations on DD between palliative care patients and health practitioners

After patients have been recruited by the HP to participate in step 3, the research team will inform them about the study. Only after these patients have signed a declaration of consent, interviews will take place at the desired location of the patient, e.g. within the care setting. A copy of the questionnaire’s response categories will be handed out to the interviewees. The interviewer will note the patients’ answers for them. Each quantitative interview will have an estimated duration of 30 to 40 min. Interviewees are free to take a break or interrupt the interview at any time. As the interview might raise emotional disturbance and/or the need for discussing some issues in more detail, we will check in with the patient the day following the interview if possible (if not, the next possible time) to ask how they feel and if there is anything they want to talk about. The patient’s health care team will also be informed that the interview is conducted. At all three measurement times, it will be checked before conducting the inquiry, whether patients are conditionally and cognitively able to participate in an interview.

#### Qualitative

In addition to the quantitative evaluation, semi-structured qualitative interviews [73, 74] with 10–15 sets of patients, their relatives and their HP trained in step 2 will be conducted to gain a deeper insight into their perception of the conversation about DD between patients and HPs [44, 75]. As one of the main outcomes is the quality of the relationship between patients and the HPs, we chose triads to account for interactional aspects. Moreover, this will allow us to obtain three perspectives on the identical care situation [76]. Criterion sampling [77] will be conducted to depict the variance of patients’ characteristics and settings.

After patients have participated in the quantitative survey, 10 to 15 of them, and in each case one of their relatives, will be asked to participate in an additional semi-structured qualitative interview. The request to attend a qualitative interview will be placed by a HP trained in step 2, who is also willing to participate in a qualitative interview. If HP, patients and relatives agree to participate, the research team will inform them about the study. Only after HP, patient and relative all have signed a declaration of consent for the triads individual interviews will be conducted at the desired location of the interviewees, e.g. within the care setting. The interviews will be recorded on tape and will have an estimated duration of 30 to 60 min. Interviewees are free to take a break or interrupt the interview at any time. As the interview might raise emotional disturbance and/or the need for discussing some issues in more detail, we will check in with the HP, patient and relative the day following the interview, if possible (if not the next possible time) to ask how they feel and if there is anything they want to talk about. The patient’s health care team will also be informed that the interviews are being conducted and optional psychological support for the interviewer and the interviewees in case of need will be ensured.

### Data analysis

#### Quantitative

The full quantitative analysis set as derived from the intention-to-treat (ITT) principle includes all patients with a valid assessment at t0 (baseline survey) and t1 (post-survey). The primary outcome “change in PDRQ-9 from t0 to t1” is analyzed by a two-sided paired t-test with a significance level of 5%. The corresponding null hypothesis is “H0: The Patient-Doctor-Relationship (measured with PDRQ-9) does not change from t0 to t1” and the alternative hypothesis “H1: There is a change in Patient-Doctor-Relationship from t0 to t1”. Additional explorative subgroup analyses (ANCOVA) are done by sex, age, socio-economic status, social inequalities and setting. The secondary outcomes and sensitivity analyses for change in PDRQ-9 from t0 to t2 are essentially analyzed along the same lines as the primary outcome, i.e. using paired t-tests. Moreover, single and multiple imputation methods are applied to analyze the impact of competing events (i.e. ADD, ADI, AaR) assuming not-at-random missing-patterns [78, 79]. Adverse events are aggregated by category and listed. Time-to-event (e.g. survival) distributions are summarized by the Kaplan-Meier method and subgroups are compared by the (stratified) log-rank test. For descriptive analyses qualitative data are summarized by count (percentage), quantitative data by mean, standard deviation and percentiles (0, 25, 50, 75, 100). To pay attention to the interrelation of various personal characteristics (intersectional theory) [80], the analysis of results will include testing the correlation of these diverse characteristics including socio-economic and cultural background as well as gender and CISP outcomes.

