### Procedure and sample

As combining qualitative and quantitative methods provides a more complete view on the research topic than including only one type of data [58, 59], we will use semi-structured interviews as well as standardized and validated questionnaires to evaluate conversations on DD between HPs and palliative care patients. Given how the intervention is still under development, this study is prospective and observatory. The study will investigate whether there is no harm caused by the intervention and will set the ground for a future randomized controlled trial (RCT).

Criteria for patient inclusion and sample heterogeneity are similar to those applied in step 1 (see Table 1) supplemented by one inclusion criterion: a life expectancy of 3 to 12 months (surprise question). Each of the 60 HPs trained in step 2 will be asked to recruit about 5 patients for the evaluation of conversations on DD. A total of 300 patients for quantitative analysis will enable us to detect even small within-group effects (with α = 5% and 1 – β = 80%, i.e. < 0.2 Cohen’s d for the whole group; in subgroups of *n* = 40 < 0.5 “moderate”). Patient sampling will be consecutive including every eligible patient fulfilling the inclusion criteria from different care settings (inpatient and outpatient, palliative, oncological, neurologic/psychiatric and geriatric wards, senior residences).

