SAHD-D – Schedule of Attitudes Towards Hastened Death German Version	Assessment of patients‘desire to hasten death	20, yes/no (true/false)	10 min	Validated in German/ Patients in specialized palliative care units
PHQ9- Patient Health Questionnaire	Facilitate detection of depression according to DSM-IV criteria	9, 4 point Likert scale (0 = Not at all, 1 = Several days, 2 = More than half the days, 3 = Nearly every day)	5 min	Validated in German/ Patients in primary care
BHS - Beck Hopelessness Scale	Assessment of hopelessness and depression	20, true/false	10 min	Validated in German
VAS - Visual Analogue Scale	Assessment of will to live	1, 100 mm-sacle from complete will to no will	Completed in seconds	–
Total		74	30–40 min	

To complete the aforementioned questionnaires, the research team will conduct personal quantitative interviews with each patient at three measurement times (1. max. 1 week before the HP-patient-conversation on DD, 2. max. 1 week following the conversation, and 3. four to 6 weeks after the conversation; see Fig. 3). At the second measurement time, patients will additionally be asked to name the content discussed during the consultation.

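### The full analysis set labelled ITT requires a valid t1, so it is a completers set, and the primary mean change and any no-harm reading can be biased by an unknown amount

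*Protocol article*

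**What the plan says.** All references are to Step 3 of the protocol article unless another section is named.

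- **Analysis set** (Data analysis, Quantitative): the set derived from the "intention-to-treat (ITT) principle includes all patients with a valid assessment at t0 (baseline survey) and t1 (post-survey".
- **Primary test** (same section): the change in PDRQ-9 from t0 to t1 "is analyzed by a two-sided paired t-test with a significance level of 5" percent.
- **Timing of t1** (Data collection, Quantitative): "2. max. 1 week following the conversation". t0 is at most one week before the conversation and t2 is four to six weeks after it.
- **Fitness check** (same section): at every measurement time "it will be checked before conducting the inquiry, whether patients are conditionally and cognitively able to participate in an interview".
- **Other analyses** (Data analysis, Quantitative): "sensitivity analyses for change in PDRQ-9 from t0 to t2 are essentially analyzed along the same lines as the primary outcome", that is, by paired t-test. The section adds single and multiple imputation for three kinds of attrition under a not-at-random assumption, and a listing of adverse events by category. The Abbreviations give the three kinds as death, illness and attrition at random.
- **Sample size** (Procedure and sample): "A total of 300 patients for quantitative analysis will enable us to detect even small within-group effects", with "1 – β = 80%, i.e. < 0.2 Cohen’s d for the whole group" and d < 0.5 in subgroups of 40. The 300 equals 60 trained practitioners times about 5 patients each.
- **Purpose** (Procedure and sample; Data analysis, Qualitative): the study is to examine whether the intervention causes no harm, and a later RCT depends on that.

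**The concern.** An intention-to-treat set is fixed by what is known at entry. This one is fixed by an event after entry: a valid t1 score. A consented patient who has t0 but then deteriorates, dies, declines the conversation, or withdraws after it is outside the primary analysis, and a paired t-test has no other way to use that patient.

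The loss is unlikely to be unrelated to outcome. t1 exists only if the conversation took place and the patient passed the fitness check, and the article itself assumes not-at-random patterns for its attrition categories. In a pre-post study without a control group, the estimate is simply the mean change of whoever is analysed, so selection after entry acts on it directly.

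Two further features bear on the no-harm question. The t0–t2 paired test is described as a sensitivity analysis, but it concerns another time point and needs a t2 score, so it cannot show how sensitive the t0–t1 result is to missing t1. And the attrition categories have no place for a patient who refuses t1 or leaves in distress after the conversation; unless classed as illness, such a patient would be counted as attrition at random.

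**Working it through.** **Inputs from the article:** two-sided alpha 5%, power 80%, N = 300, subgroup n = 40, paired t-test on change. **Assumed, because the article gives no figures:** the share m without t1, and the gap in mean change between completers and those lost, in SD units of the change score. Patients are treated as independent, as the paired t-test does.

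**1. The plan's own figures.** Detectable d = (z₀.₉₇₅ + z₀.₈₀)/√n.
- n = 300: 2.802/17.32 = 0.162 (exact noncentral t: 0.162).
- n = 40: 2.802/6.325 = 0.443 (exact: 0.454).

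Both meet the stated bounds of 0.2 and 0.5, provided that all 300, or all 40, have both assessments.

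**2. Effect of losing t1 on precision** (exact t).

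| Loss at t1 | Analysed of 300 | Detectable d | Analysed of 40 | Detectable d |
|---|---|---|---|---|
| 0% | 300 | 0.162 | 40 | 0.454 |
| 10% | 270 | 0.171 | 36 | 0.480 |
| 20% | 240 | 0.182 | 32 | 0.511 |
| 30% | 210 | 0.194 | 28 | 0.549 |
| 40% | 180 | 0.210 | 24 | 0.597 |

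The smallest n for d = 0.2 is 199, so the whole-group claim tolerates a loss of (300 − 199)/300, about 33%. The smallest n for d = 0.5 is 34, so a subgroup of 40 enrolled misses its bound once fewer than 34 have t1, that is, once more than 6 of 40 (15%) are lost.

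**3. Possible bias.** Completers' mean minus the mean over all enrolled = m × (mean change of completers − mean change of those lost).

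| Loss m | Gap 0.25 SD | Gap 0.5 SD | Gap 1.0 SD |
|---|---|---|---|
| 10% | 0.025 | 0.05 | 0.10 |
| 20% | 0.05 | 0.10 | 0.20 |
| 30% | 0.075 | 0.15 | 0.30 |

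At 20% loss and a gap of 0.5 SD the shift is 0.20 × 0.5 = 0.10 SD, half of the 0.2 named in the sample-size statement. If those lost would have done better than completers, the sign reverses.

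**4. What that would do to the test.** Suppose the true mean change over all enrolled is zero and those lost are 0.5 SD worse than completers. The completers' mean is then m × 0.5, and the paired t-test shows a significant improvement with probability about 13% (m = 10%, n = 270), 34% (20%, n = 240) or 58% (30%, n = 210).

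**5. How much loss could be death?** t0 and t1 are at most about two weeks apart. If median survival were 12 months (52 weeks) or 3 months (13 weeks) with constant hazard (an assumption suggested by the entry criterion of 3 to 12 months), deaths in that window would be 1 − 0.5^(2/52) = 2.6% to 1 − 0.5^(2/13) = 10.1%. Illness, refusal and conversations not held may therefore matter more than death at t1.

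**The case against.** The strongest reply is that the article does address missing outcomes. It plans single and multiple imputation under not-at-random assumptions, naming death and illness. A reader might infer from the set definition that missing t1 is ignored; that is not so. This point stands as a partial mitigation. It does not alter the set, its label or the primary test.

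Second, bias is possible, not demonstrated. No attrition rate is stated, the interval is short, and the outcome is within-patient change, so being sicker or less satisfied at t0 does not by itself imply a worse change. A reader might infer a bias towards improvement; the article supports neither the direction nor the size. This stands.

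Third, a mixed model is no cure. It assumes missing-at-random. If loss is unrelated to t0 and those lost have no t2, the model gives them the same expected change as completers, and a not-at-random gap like that in the example remains. It also implies t1 values for patients who have died. This stands and shapes the fix.

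Fourth, patients distressed by the conversation are not wholly hidden. Adverse events are listed, and in Step 2 practitioners are asked to reflect on burden in these consultations; neither is said to depend on t1. Patients who never had the conversation cannot conceal harm from it. So the claim is limited to the primary estimate and to the attrition categories.

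Fifth, this is a formative single-group study with no randomised comparison for ITT to protect. That lowers the stakes, but it does not make the label correct or the selection harmless.

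**Conclusion.** The point holds on the text. A set that needs a valid t1 is a paired-data set and should not be called ITT. Because t1 depends on the conversation and on fitness for interview, and the article expects not-at-random losses, the primary mean change and any no-harm statement drawn from it can be biased. The size is unknown: 0.10 SD at 20% loss and a 0.5 SD gap, and from 0.025 to 0.30 SD over the assumed ranges of 10% to 30% loss and gaps of 0.25 to 1.0 SD.

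A reader might also infer that the study is underpowered because 300 is both the number recruited and the number in the power statement. For the whole group that is not supported: d < 0.2 holds up to about 33% loss if patients are independent. Only the subgroup bound is fragile, failing once fewer than 34 of 40 have t1.

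**What to change.** 1. Define the full analysis set as all consented patients with a valid t0.
2. Estimate the t0–t1 change with a method that uses every available PDRQ-9 score, for example a repeated-measures mixed model over t0, t1 and t2 with the t0–t1 contrast as primary.
3. Tie the planned not-at-random imputation explicitly to missing t1 and report it beside the primary estimate as the key sensitivity analysis, with deaths handled separately.
4. Keep the t0/t1 paired t-test, labelled as a completers analysis.
5. Call the t0–t2 change a secondary outcome, not a sensitivity analysis.
6. Report patients without t1 by reason, with a category for refusal or distress after the conversation, so that these are not filed under attrition at random.

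The cost is a change of wording, a standard model on scores already being collected, and recording the reason for each missing t1. The small downside is that the mixed model relies on missing-at-random, so it does not replace the not-at-random analyses; both are needed.

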### Procedure and sample

In implementing the training courses, the results of our preliminary work can be referred to ([name]*, [name]*, [name], [name], [name], [name], [name], [name], [name], [name]. How to deal with a patient´s desire for hastened death: Development of a teaching course for health professionals in palliative care, submitted; [name]*, [name]*, [name], [name], [name], [name]. Let’s talk about the desire to die - evaluation of a training course for health professionals, in preparation). Within a previous project, the training concept was developed, piloted and evaluated. Based on the evaluation, the curriculum was revised. The CISP will be applied continuously during the training.

Five training courses will be conducted, each with 12 health care professionals from various professions and disciplines as well as hospice staff members. HPs will be purposefully sampled; eligibility criteria for participating in the course are presented in Table 3.

**Table 3 Tab3:** Criteria for course participation

Participation Criteria
a) Belonging to one of the multi-professional occupational groups in palliative care (e.g. physicians, nurses, social workers, psychologists, hospice staff members)
b) Involvement in direct in- or outpatient specialist or general palliative care for at least 3 years
c) Adequate German language skills

Course participants will be recruited from the Cologne region. This geographical limitation allows an evaluation of the training impact by personal face to face interviews with HPs, patients, and relatives in step 3. Taking part in the training course is voluntary and free of charge for HPs. Following the courses, participants will be asked to use the CISP in addition to the competences learned in the training course, when discussing DD in routine consultations. By participating in the training course, HPs explicitly agree to recruit patients they will discuss a DD with to be enrolled in step 3 of this study.

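### The paired t-tests treat about 300 patients as independent although they are nested in 60 trained practitioners, so the 5% level is exceeded if change differs between practitioners

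*Protocol article*

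**What the plan says.** The primary outcome, change in PDRQ-9 from t0 to t1, "is analyzed by a two-sided paired t-test with a significance level of 5"% (Protocol article, Step 3, Data analysis, Quantitative). The same section says that the secondary outcomes and the t0 to t2 sensitivity analyses "are essentially analyzed along the same lines as the primary outcome, i.e. using paired t-tests".

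The structure of the sample is set earlier. In Step 2, Procedure and sample: "Five training courses will be conducted, each with 12 health care professionals", which makes 5 × 12 = 60 health practitioners (HPs). In Step 3, Procedure and sample: "Each of the 60 HPs trained in step 2 will be asked to recruit about 5 patients".

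The sample-size statement in the same Step 3 section reads "A total of 300 patients for quantitative analysis will enable us to detect even small within-group effects", "with α = 5% and 1 – β = 80"%. It gives two bounds: "< 0.2 Cohen’s d for the whole group" and "in subgroups of *n* = 40 < 0.5".

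Neither the test nor the sample-size statement mentions an HP effect, an ICC or a design effect.

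**The concern.** A paired t-test on 300 changes takes each patient's change as independent of every other. Here about five patients share one HP, who conducts the conversation being evaluated. The HPs come from several professions, disciplines and care settings. The section on qualitative data collection in Step 3 describes a main outcome as the quality of the relationship between patients and HPs. Patients of the same HP therefore share the person who delivers the intervention and, on that description, the person whose relationship is rated.

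Subtracting t0 from t1 removes whatever is constant about an HP, such as being well liked at both times. It does not remove variation between HPs in how much the conversation moves the score, and that change is the endpoint. If HPs differ in this respect, the t-test understates the standard error and a nominal 5% test rejects too often. Because the same test is prescribed for the secondary and t0 to t2 analyses, they share the problem.

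**Working it through.** **Inputs from the protocol article.** Two-sided α 5%, power 80%, n = 300, subgroups of 40, 60 HPs with m = 5 patients each.

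**Input assumed.** The ICC of the change score is not given. A range of 0.02 to 0.20 is shown.

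**Step 1: reproduce the stated bounds for independent patients.** For a paired test, d = (1.960 + 0.842)/√n.
- n = 300: 2.802/√300 = 0.162 (the exact t calculation also gives 0.162). This is below 0.2.
- n = 40: 2.802/√40 = 0.443 (exact t: 0.454). This is below 0.5.
- For d = 0.2, 199 patients would suffice; 300 give 93% power.

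Both stated bounds reproduce under independence.

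**Step 2: add clustering with all 300 analysed.** Design effect DE = 1 + (m − 1) × ICC = 1 + 4 × ICC. Effective n = 300/DE. True type I error of the unadjusted test = 2 × [1 − Φ(1.96/√DE)]. Detectable d under a valid analysis = 0.162 × √DE.

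| ICC (assumed) | DE | Effective n | True type I error | SE should be larger by | Detectable d |
|---|---|---|---|---|---|
| 0.02 | 1.08 | 278 | 5.9% | 1.04 | 0.168 |
| 0.05 | 1.20 | 250 | 7.4% | 1.10 | 0.177 |
| 0.10 | 1.40 | 214 | 9.8% | 1.18 | 0.191 |
| 0.20 | 1.80 | 167 | 14.4% | 1.34 | 0.217 |

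Worked line for ICC 0.10: DE = 1 + 4 × 0.10 = 1.40; √1.40 = 1.183; 1.96/1.183 = 1.657; two-sided tail 9.8%.

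**Step 3: check by simulation.** In 20,000 null data sets of 60 × 5 patients per ICC value, the unadjusted t-test rejected in 7.3% (ICC 0.05), 10.0% (0.10) and 14.6% (0.20). A t-test on the 60 HP means rejected in 4.9% to 5.1%. Analysing at the level of the HP restores the nominal level.

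**Step 4: when does d < 0.2 fail?** It fails when 0.162 × √DE reaches 0.2, that is at DE = (0.2/0.1617)² = 1.53, so ICC = 0.53/4 = 0.13. With a t reference on 59 degrees of freedom the limit is 0.12. Power at d = 0.2 is 89% at ICC 0.05, 83% at 0.10 and 73% at 0.20.

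**Step 5: fewer evaluable patients.** The analysis set requires valid t0 and t1 assessments. If 240 were analysed (an assumed figure, 4 per HP), ICC 0.10 gives DE = 1 + 3 × 0.10 = 1.30 and d = 2.802 × √(1.30/240) = 0.206. ICC 0.05 gives 0.194. With independence, 240 patients already give 0.181, so part of this erosion comes from the smaller number and not from clustering.

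**The case against.** Several arguments weigh against making much of this.

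- **The correlation is not demonstrated.** The relevant ICC is that of the change score. Pairing has already taken out stable HP differences in level, so this ICC may be small. At 0.02 the type I error is only 5.9%. This stands as a limit on the size of the problem. It does not rescue the test, because the analysis assumes an ICC of exactly zero in a study where the HP delivers the intervention.
- **The detectable effect.** A reader might infer that the sample-size claim is therefore false. The document does not support that. It states only a bound of 0.2, and 300 patients leave a reserve that absorbs a design effect of about 1.5. Failure at a low ICC requires attrition figures that the document does not give, and the text speaks of 300 patients for the quantitative analysis.
- **Harm.** A reader might also infer that the study's conclusion about absence of harm is compromised. No test or margin is named for that conclusion, and adverse events are only categorised and listed. In a two-sided test, a standard error that is too small would flag deterioration too readily; it would not produce false reassurance from a non-significant result.
- **Confidence intervals.** The analysis section names none, so intervals that are too narrow are an inference and not a stated feature of the plan.
- **The study is observational, single-group and formative.** Clustering leaves the estimated mean change unbiased and affects only its precision. This argues against calling the point critical. It does not remove it, since the protocol sets a formal null hypothesis and a 5% level, and the test prescribed does not keep that level if the ICC is positive.

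**Conclusion.** The point holds for the test. The protocol fixes an analysis that ignores the nesting of about 300 patients in 60 HPs. Any positive ICC of the change score then pushes the type I error above 5%: to about 7% at ICC 0.05, 10% at 0.10 and 14% at 0.20, assuming five patients per HP. Unequal recruitment would raise these figures somewhat. With a coefficient of variation of cluster size of 0.6 (assumed) and ICC 0.10, DE = 1 + [(1 + 0.36) × 5 − 1] × 0.10 = 1.58 and the error is 11.9%.

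It does not hold as a claim that the stated detectable effect is wrong. That bound is correct for independent patients and survives clustering up to an ICC of about 0.12 to 0.13 with 300 analysed. It is conditional on an ICC and an evaluable number that the text does not state.

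The nesting and the prescribed test are certain from the document; the size of the consequence rests on the assumed ICC. This is a point that should be fixed, of moderate weight.

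**What to change.** In Step 3, Data analysis, Quantitative, replace the paired t-test for the t0 to t1 change by one of two analyses, chosen in advance:

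- a linear mixed model for the change with a random intercept for HP; or
- the mean change with standard errors clustered on HP.

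Either should use small-sample degrees of freedom suited to 60 clusters. Apply the same method to the secondary outcomes and to the t0 to t2 change.

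In Step 3, Procedure and sample, state the detectable effect together with the assumed ICC and the number of patients expected to have valid t0 and t1 assessments. With 300 analysed, for example, it is 0.177 at ICC 0.05 and 0.191 at ICC 0.10. The authors should choose and justify their own values.

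The cost is a change of wording, a somewhat larger standard error if the ICC is positive, and a slightly less favourable stated effect. No extra patients or data are needed, because HPs recruit the patients and the link is known. If the ICC proves close to zero, the result will barely differ from the paired t-test.

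### For its intersectional aim the Step 3 analysis names only correlation tests, which do not show whether change depends on combinations of patient characteristics

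*Protocol article*

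**What the plan says.** Under Step 3, Data analysis, Quantitative, the protocol article gives the purpose as "To pay attention to the interrelation of various personal characteristics (intersectional theory"). For that purpose it says that "the analysis of results will include testing the correlation of these diverse characteristics including socio-economic and cultural background as well as gender and CISP outcomes". The method named is thus "testing the correlation of these diverse characteristics" and the outcomes. No product term, cross-classified grouping or other joint model is mentioned.

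Earlier in the same paragraph stands a separate analysis by patient characteristics: "Additional explorative subgroup analyses (ANCOVA) are done by sex, age, socio-economic status, social inequalities and setting". It neither states nor excludes interactions between these factors, and its list does not name cultural background, which the correlation sentence does.

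Gender and social inequality also appear in the Abstract, in the third aim at the end of the Background, and among the expected benefits in the Discussion. Each time they are aspects to be considered or attended to. The sample size statement (Step 3, Procedure and sample) concerns change within a group only: "A total of 300 patients for quantitative analysis will enable us to detect even small within-group effects".

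**The concern.** Purpose and named method do not match. An intersectional question asks whether the outcome differs by combination of characteristics, for instance whether the effect of socio-economic status on change differs between women and men. The sentence on correlation can be read in two ways:

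- **Characteristics correlated with outcomes.** This gives the marginal association of each characteristic, averaged over the others.
- **Characteristics correlated with one another.** This shows how they cluster in the sample and says nothing about outcome.

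Neither gives a joint effect. If an analysis plan followed the sentence literally, opposite changes in different combinations could average out and be reported as no association. Several separate correlation tests would also invite chance findings. What is at stake is one exploratory aim, not the main result.

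**Working it through.** **1. Inputs.** From the article: 300 patients, two-sided 5% level, 80% power, and detectable within-group effects stated as below 0.2 (whole group) and below 0.5 (subgroups of 40). Assumed, because the article gives neither: the split of patients by gender and socio-economic status, and the number analysable after attrition. Effects are in SD of the change score, and patients are treated as independent. The multiplier is 1.960 + 0.842 = 2.802.

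**2. The plan's own figures.** For a paired t-test, detectable d = 2.802 / √n.

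- n = 300: 2.802 / 17.32 = 0.162, below 0.2.
- n = 40: 2.802 / 6.325 = 0.443 (0.454 with the noncentral t), below 0.5.

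Both statements reproduce. They concern change within one group, not differences between groups or combinations.

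**3. Can single correlations miss a joint effect?** Take four equal cells of 75. Let mean change be +0.2 SD in low-status women and high-status men, and −0.2 SD in the other two cells. Each gender averages 0 and each status group averages 0, so both marginal correlations are 0. The interaction contrast is (0.2 − (−0.2)) − (−0.2 − 0.2) = 0.8 SD.

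- Standard error of the contrast: √(4/75) = 0.231 SD.
- Power of the interaction test: Φ(0.8/0.231 − 1.96) = Φ(1.50), about 93%.
- Simulation (4,000 runs, 300 patients): the gender correlation was significant in 4.7% of runs and the status correlation in 4.9%, which is chance level. The product term was significant in 93%.

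This pattern is deliberately extreme. It proves the principle and does not forecast these data.

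**4. What an interaction term could detect.** Detectable contrast = 2.802 × √(Σ 1/n_cell).

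| Analysed | Split (gender by status) | Cells | Detectable contrast | Power for 0.5 SD |
|---|---|---|---|---|
| 300 | 50/50 by 50/50 | 75, 75, 75, 75 | 2.802 × √(4/75) = 0.65 SD | 58% |
| 300 | 50/50 by 30/70 | 45, 105, 45, 105 | 2.802 × √(2/45 + 2/105) = 0.71 SD | 51% |
| 300 | 50/50 by 20/80 | 30, 120, 30, 120 | 2.802 × √(2/30 + 2/120) = 0.81 SD | 41% |
| 200 | 50/50 by 50/50 | 50, 50, 50, 50 | 2.802 × √(4/50) = 0.79 SD | 42% |
| 200 | 50/50 by 30/70 | 30, 70, 30, 70 | 2.802 × √(2/30 + 2/70) = 0.87 SD | 37% |
| 200 | 50/50 by 20/80 | 20, 80, 20, 80 | 2.802 × √(2/20 + 2/80) = 0.99 SD | 29% |

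For comparison, a main effect of gender with 150 against 150 is detectable at 2.802 × √(2/150) = 0.32 SD. Even in the best case the detectable interaction is four times the whole-group within-group figure (0.647 / 0.162 = 4.0).

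**The case against.** A reader might infer that the study cannot answer its own gender-by-social-inequality question. The article does not support that, for three reasons.

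- It poses no such question. The Abstract, aims and Discussion speak of considering or attending to these aspects, and the only formal hypothesis concerns the PDRQ-9 change from t0 to t1.
- The wording on correlation is open. It says what the analysis will include, does not say that characteristics are taken one at a time, and may use correlation loosely for association.
- The planned exploratory ANCOVA covers sex, age, socio-economic status, social inequalities and setting, and a model of that kind can carry interactions. The qualitative strand also compares by gender and socio-economic status.

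It can be added that exact model terms are commonly left to a full protocol or analysis plan that is not shown, that the crossover example is a worst case for correlations, and that the alternative detects only large interactions.

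Much of this stands. It rules out the stronger reading and limits the point to an exploratory aim. It does not remove the mismatch. The article is not silent: it ties a named purpose to a named method, and on either reading simple correlations do not serve that purpose. The ANCOVA is described as subgroup analysis, without stated interactions, and is not linked to the intersectional aim. The qualitative comparison rests on 10–15 triads and cannot estimate joint effects. That the ANCOVA could carry the interactions mainly shows how small the remedy is.

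**Conclusion.** The point holds as a minor mismatch between stated purpose and named method. Simple correlations, with outcome or among the characteristics, do not show whether change depends on combinations of characteristics. The primary analysis and the within-group sample size statement are unaffected.

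The limit on what any better method can deliver is substantial. With 300 analysed in equal cells, 80% power needs a contrast of about 0.65 SD. The figure is about 0.7 to 0.8 SD under the assumed uneven splits, and about 0.8 to 1.0 SD with an assumed 200 analysable patients. These figures rest on the assumed cell sizes, on independent patients and on the SD of the unadjusted change score. Baseline adjustment could improve them somewhat, by an amount that the article does not allow one to calculate.

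**What to change.** For the intersectional aim, replace the correlation tests by the exploratory ANCOVA already planned, specified as follows:

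- adjust for the baseline score and add cultural background to the factors;
- include a short list of two-way interactions, fixed before the data are seen, such as gender by socio-economic status;
- report each interaction estimate and the cell means with 95% confidence intervals, labelled exploratory;
- state the detectable interaction size (about 0.65 SD at best) and that a non-significant interaction is not evidence of no difference.

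Correlations among the characteristics may stay as a description of the sample. The cost is a little more analysis work and no new data. The drawback is wide intervals, which the report should state openly.
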